### Interventions

4.5

#### Arrangement for intervention

4.5.1

All researchers in this study will be trained beforehand. Participants will be instructed by trained researchers on how to use their medication and their involvement in the study.

#### Lifestyle intervention

4.5.2

Subjects in both groups of the study will receive dietary, lifestyle, and exercise advice from researcher. This advice is according to the 2017 China Type 2 Diabetes Prevention Guide.

#### Traditional Chinese medicine intervention

4.5.3

All participants in the treatment group will visit the researchers once every month, when the same Chinese doctor will examine them using four TCM diagnostic methods including inspection, listening and smelling, inquiry, and pulse measurement and palpation. Shenqi compound is composed of 8 Chinese herbs: ginseng, astragalus, raw radix rehmanniae, trichosanthin, dogwood, yam, salvia, and wine rhubarb. Ginseng and astragalus supplement the vitality together as the remedy. The four medicines are used in cooperation with each other to supplement the deficiency of yin and jin of the lungs, spleens, and kidney. Salvia miltiorrhiza and wine rhubarb are used as adjuvants to promote blood circulation and remove blood stasis. Shenqi compound regulates the body's energy metabolism and reduces blood glucose fluctuation, which is a good recipe for clinical treatment of type 2 diabetes with lower extremity atherosclerosis. At present, it has been included in the “Diagnosis and Treatment Program for Diabetes” of the Chinese Traditional Medicine Clinical Research (Diabetes) Base. The test drug is a Chinese medicine formula granule produced by Sichuan Green Pharmaceutical Technology Development Co., Ltd. Certification and quality control by director of the department of pharmacy department in the Teaching hospital of Chengdu University of TCM. Usage instructions suggest consuming the granules three times a day one lattice each time, by boiling with water before meals, stirring, covering, and sealing for 3 to 5 min. The main ingredients of placebo are beta-cyclodextrin and artificial food colors. Shenqi compound and placebo are both fried-free granules, are similar in packaging, appearance, and shape. Participants are not allowed to take other drugs during the 8-week study period. Each participant will receive 28 boxes of Chinese medicine formula granules. Participants will be asked to record the changes in their symptoms daily using a form reviewed by a researcher once every month.

#### Randomization

4.5.4

The randomization sequence will be generated according to the PROCPLAN procedure statements of the SAS software package.

According to the 1:1 random arrangement of the treatment and control group, 30 cases in each group are categorized using random distribution cards, and the subjects are assigned to each group according to a predetermined random number.

#### Allocation concealment

4.5.5

The random number table will be generated by a designated researcher using the SAS system, and the researcher will not participate in the selection or recruitment of participants.

#### Blinding

4.5.6

Considering the unique characteristics of the TCM methods used in this trial, it would be difficult to blind the researchers administering the TCM treatments and the participants. However, the researchers responsible for the statistical analyses will be blind to the grouping information.

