### Groups

4.4

Participants will be divided into two groups: the treatment and control groups. Their basic treatment can maintain the original plan, which includes a hypoglycemic regimen comprising acarbose + insulin detemir, along with antihypertensive drugs, such as ACEI, ARB, diuretics, calcium antagonists, and β-blockers. Following which lipid-lowering drugs like atorvastatin will be administered.

Control group: Basic treatment + Chinese medicine placebo.

Treatment group: Basic treatment + Shenqi compound. One bag of the test drug three times a day, boiled with water before meals, stirred, covered, and sealed for 3 to 5 min, for a period of 4 weeks. Followed by observation for 8 weeks.

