#### Traditional Chinese medicine management

4.10.2

Participants will receive formula granules of Shenqi compound produced by Sichuan Green Pharmaceutical Technology Development (fixed prescription granules). Usage: one bag at a time, three times a day. Boil with water before meals, stir, cover, and seal for 3 to 5 min before consumption.

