Compared to other studies, this study focuses on influencing blood glucose fluctuations and improving lower extremity atherosclerosis. Here, we want to further study the efficacy of Shenqi Compound in influencing the blood glucose fluctuation in type 2 diabetes with lower extremity atherosclerosis. Since blood glucose fluctuations are prone to damage the vascular endothelium and are a risk factor for lower extremity atherosclerosis,^[21]^ the effect of Shenqi Compound on arterial color Doppler ultrasound is evaluated as the main outcome indicator. Because blood glucose fluctuations are important predictors of vascular complications of diabetes,^4^ the evaluation of blood glucose fluctuations and islet β-cell function indicators will be calculated by formulae as secondary outcome indicators. Since HbA1c variability represents long-term blood glucose fluctuations,^[3]^ the effect of Shenqi compound on glycated hemoglobin is also evaluated. Furthermore, blood glucose fluctuation and lower extremity atherosclerosis are closely related to disorders of lipid metabolism,^[22]^ it is also imperative to evaluate the effects of Shenqi compound on blood lipids. Inflammatory cells play an important role in the occurrence and development of lower extremity atherosclerosis, due to which NLR is closely related to the formation of AS, subsequently highlighting the need to the effect of Shenqi compound on inflammation indicators, specifically NLR. Evaluating the severity of lower extremity atherosclerosis by detecting NLR clinically would be essential in providing a powerful reference for the refinement and management of patients.^[7]^ Bias will be minimized by adopting a rigorous methodology. Despite the fact that this study is an open label trial, some measures will be considered to strengthen quality control, considering the nature of RCT multicenter trial and CER design. To avoid the bias from the researchers, an independent investigator will be assigned in each research center as the contact person to preserve and record the randomization information. Therefore, clinical researchers will have no influence on enrollment or randomization. This study strives to effectively improve the blood glucose fluctuation and delay type 2 diabetes with lower extremity atherosclerosis, which has significant social benefits.

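### A look-alike placebo is supplied, yet the trial is called open label; only the analysts are named as blind, and masking of the ultrasound reader is not stated

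*Protocol article*

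**What the plan says.** **Placebo.** Section 4.4 (Groups) of the protocol article defines the comparator: "Control group: Basic treatment + Chinese medicine placebo". Section 4.5.3 (Traditional Chinese medicine intervention) describes the products: "Shenqi compound and placebo are both fried-free granules, are similar in packaging, appearance, and shape". Section 4.10.2 (Traditional Chinese medicine management) describes the active product as "fixed prescription granules".

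**Blinding.** Section 4.5.6 appeals to the special character of the TCM methods and says that "it would be difficult to blind the researchers administering the TCM treatments and the participants". The only masking it provides is that "the researchers responsible for the statistical analyses will be blind to the grouping information". The Discussion (section 5) is explicit: "Despite the fact that this study is an open label trial". It adds that an independent person at each centre will hold the randomization information, so that clinical researchers cannot influence enrolment or randomization.

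**Contact.** Section 4.5.3 also states: "All participants in the treatment group will visit the researchers once every month, when the same Chinese doctor will examine them", using the four TCM diagnostic methods. No matching sentence is written for the control group.

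**The concern.** A placebo with the same look as the active product is normally supplied so that participants and staff need not know the allocation. If they do know it, the placebo loses much of its purpose. It can no longer balance expectation between the arms, and it cannot protect outcomes that someone has to judge.

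Several outcomes here depend on judgement. The primary outcome is arterial colour Doppler ultrasound, in which an operator assesses intimal thickness, sclerosis, plaque and stenosis (section 4.8.1). Others are SF-36 (4.8.3), the daily symptom form (4.5.3), adverse-event severity and causality (4.9.5, 4.9.7) and exit for poor effect (4.6.6). Blinding the analysts cannot repair data that were already recorded with knowledge of the arm.

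If the primary comparison favoured Shenqi compound, the trial could not separate an effect of the compound from an effect of knowing who received it. The Abstract says the trial is needed because high-quality clinical evidence is lacking, so this matters for its stated purpose.

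**Working it through.** The plan states no figure on this point, so the main check is to set the sections side by side.

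1. *Does the treatment itself reveal the arm?* The active product is a fixed prescription, and sections 4.5.3 and 4.10.2 give one schedule of use that does not vary by patient. The placebo is similar in packaging, appearance and shape. Nothing in these sections requires the treating doctor to know the arm in order to prescribe or dispense.
2. *Does the stated reason cover this?* Section 4.5.6 refers only to the character of TCM methods. That would explain a difficulty with, say, individually tailored prescriptions. It does not explain one with fixed look-alike granules.
3. *Who is masked?* Section 4.5.6 names the statistical analysts. No section says whether the ultrasound reader is masked. The independent contact in section 5 is offered as protection for enrolment and randomization, not for outcome assessment.
4. *Is contact equal?* The monthly four-method examination by the same doctor is written for the treatment group. The monthly review of the symptom form (4.5.3) and the measurements at baseline, w4, w8, w12 and w24 (4.9.1) are not limited to one arm. The documented difference is therefore the TCM examination, not the existence of regular visits.

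**Illustration of size.** The documents do not say how large a bias might be, so the shift d below is an assumption shown as a range.

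- Inputs: 30 per group (4.5.4) and 20% loss (4.5.7), so n = 30 × (1 − 0.20) = 24 per arm. True effect zero; two-sided t test at 0.05 with 2 × 24 − 2 = 46 degrees of freedom and critical value 2.013.
- Noncentrality = d × √(n/2) = d × √12 = 3.464 d.
- Error rate = P(|T| > 2.013), where T is noncentral t with that noncentrality.

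| Assumed spurious shift d (SD) | Noncentrality | Error rate, 24 per arm | Error rate, 30 per arm |
|---|---|---|---|
| 0 | 0 | 5.0% | 5.0% |
| 0.2 | 0.693 | 10.4% | 11.9% |
| 0.3 | 1.039 | 17.4% | 20.8% |
| 0.4 | 1.386 | 27.4% | 33.2% |

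The last column repeats the calculation with no losses (58 degrees of freedom). A larger sample does not remove the bias; it makes a false positive more likely.

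**The case against.** There are five fair points on the other side.

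- **Matching is partial.** Only packaging, appearance and shape are claimed. The placebo is mainly beta-cyclodextrin and food colours, against eight herbs prepared with boiling water. Taste or smell may reveal the arm to some participants, so full double-blinding may not be achievable. This stands. It is a reason to describe the blinding as possibly incomplete, but not a reason to disclose allocation.
- **Visits.** A reader might infer that only the Shenqi arm attends monthly. The text does not support that: the diary review and the w4, w8 and w12 measurements appear to apply to both arms, and the visit schedule (Figure 1) is not visible here. Only the TCM examination is written for one arm.
- **Ultrasound reader.** A reader might infer that the reader knows the allocation. The article does not say so, and the full protocol may specify masking. What can be said is that section 4.5.6, which sets out who is blind, does not include the reader.
- **Worth of the placebo.** It would be too strong to say that the placebo controls for nothing. Section 4.5.6 calls blinding difficult and does not say that participants are told their arm. HbA1c, lipids, CRP, IL-6 and NLR leave little room for reader or reporting bias, although behaviour could still affect them. Nor do the documents say that glucose is self-measured, so it should not be listed as a self-reported outcome.
- **Size.** The shifts are assumed, and the full analysis set carries forward the final observation, so the analysed number may exceed 24 per arm. Both points are correct; the table therefore starts at zero and also shows 30 per arm.

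None of these explains why look-alike fixed granules should be given open label.

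**Conclusion.** The inconsistency holds and nothing else in the article resolves it. Sections 4.4, 4.5.3 and 4.10.2 supply the means to withhold allocation, while section 4.5.6 and the Discussion give up on doing so without an adequate reason. Expectation and assessment bias therefore remain possible in the operator-read primary outcome, SF-36, the symptom diary, adverse-event judgements and withdrawal for poor effect. The one-arm TCM examination adds a smaller imbalance in attention.

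The size cannot be derived from the documents. Under assumed shifts of 0 to 0.4 SD with 24 per arm, the two-sided error rate lies between 5% and 27%. The conclusion about the design does not depend on those values. Because no later analysis can undo such bias, the point should be settled before enrolment.

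**What to change.** Reconcile sections 4.5.3, 4.5.6 and 5 as follows.

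1. Dispense Shenqi compound and placebo in coded, identically labelled kits, with the code held by the independent contact that section 5 already assigns to each centre.
2. State in section 4.5.6 that allocation is withheld from participants, treating doctors and the existing ultrasound readers, as well as from the analysts.
3. Word the monthly four-method examination in section 4.5.3 for both groups.
4. Remove the open-label description from the Discussion. If taste or smell may unblind some participants, still withhold allocation and mask the ultrasound reader, and describe the blinding as potentially incomplete.

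If the sponsor believes that the granules cannot be given without disclosure, the protocol should give the specific reason and still mask the ultrasound reader.

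The cost is kit coding, an emergency code-break procedure, the monthly TCM examination for controls and the rewording. The placebo and the independent contacts are already in the plan. Controls appear to be measured at baseline, w4 and w8 already, so few extra visits should be needed.

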#### Sample size

4.5.7

We aim to select a sample size estimation method when comparing the two sample means. The following calculation formula may be used when the sample number of the test group and the control group is expected to be equal:
 
[figure not shown]

Here, n represents the estimated sample size of each test group, μα and μβ are the μ values corresponding to α and β, where μα represents the μ value of the probability of a type I error, μβ represents the μ value of a type II error, and δ is consistent with the required degree of discrimination, and σ is the standard deviation of the population. In the formula, μα and μβ can be calculated from the degree of freedom table of the *t*-boundary value υ = ∞−. If the test is required to have a probability of making a type I error >5% and a probability of making a type II error >10%, that is 0.05, β = 0.1, t value table indicated that *t*0.05 = 1.64, *t*0.1 = 1.28, refers to the relevant Chinese medicine treatment of type 2 diabetes blood sugar fluctuations, diabetes combined with lower extremity atherosclerosis.^[11,12]^ The standard deviation of indicator of blood glucose fluctuation–blood glucose (SDBG) in the literature will be set as the clinical efficacy observation, with SDBG <2.0 mmol/L being normal, then σ = 2.41, δ = 2.0. Here, the value of n brought into the formula is about 24.76, so the minimum sample size for this test is 50 cases. The estimated lost follow-up rate is 20%, and the final number of cases included is 60.

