**Methods::**

A multicenter RCT will be implemented in this study for a 32-week study period (8 weeks for intervention and 24 weeks for follow-up). Participants will be recruited from the Teaching Hospital of Chengdu University of TCM, Mianyang Hospital of TCM, and Shuangliu Hospital of TCM. Sixty participants will be randomly divided into a treatment group (basic treatment combined with traditional Chinese medicine Shenqi Compound) or a control group (basic treatment combined with Chinese medicine placebo) with 30 participants in each group. Patients will be selected considering the following inclusion criteria: age between 35 and 65 years, and a positive diagnosis for type 2 diabetes with lower extremity atherosclerosis and TCM syndromes. Primary outcome indicator is an arterial color Doppler ultrasound. Secondary outcome indicators include: blood glucose fluctuation indicators (MBG, SDBG, LAGE), islet β-cell function evaluation indicators (Homa-IR, Homa-islet, SG, SCP), inflammation indicators (NLR, CRP, IL-6), blood lipids, and HbA1c. Safety index includes vital signs (T, P, R, BP), blood, urine, stool routine, liver and renal function, electrocardiogram, and adverse event records. The endpoint event is defined as the presence of gangrene in the lower limbs.

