#### Primary outcomes

4.8.1

1.Arterial color Doppler ultrasound. (Assess arterial intimal thickness, degree of sclerosis, plaque, stenosis)^[16,17]^

Arterial color Doppler ultrasound will be tested at Visits 0 and 8.

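### The sample size is calculated for SDBG, a secondary outcome, so its 90% power is not established for the Doppler primary outcome, and delta = 2.0 has no printed justification as a between-arm difference

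*Protocol article*

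**What the plan says.** The Abstract states: "Primary outcome indicator is an arterial color Doppler ultrasound". Section 4.8.1 repeats this and lists what is examined: "Arterial color Doppler ultrasound. (Assess arterial intimal thickness, degree of sclerosis, plaque, stenosis". The Abstract places SDBG lower: "Secondary outcome indicators include: blood glucose fluctuation indicators (MBG, SDBG, LAGE". Section 4.8.2 does the same, and the Discussion confirms the ranking: "the evaluation of blood glucose fluctuations and islet β-cell function indicators will be calculated by formulae as secondary outcome indicators".

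Section 4.5.7 uses the formula for comparing two means. Its variable is SDBG, which "in the literature will be set as the clinical efficacy observation". The error rates are "that is 0.05, β = 0.1", with critical values 1.64 and 1.28. The effect inputs are "SDBG <2.0 mmol/L being normal, then σ = 2.41, δ = 2.0". The result is about 24.76 per arm, a minimum of 50 in total, and 60 after allowing for 20% loss. The section cites literature on glucose fluctuation and on lower extremity atherosclerosis, but no ultrasound quantity enters the formula. The article contains no other power or sample-size figure.

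**The concern.** A sample-size calculation should show that the trial can answer its primary question. Here the calculation concerns one variable and the primary question another. A difference of 2.0 mmol/L in SDBG gives no information about the size of effect, or the variability, to expect on an ultrasound measure. If the Doppler comparison is null, a reader who sees beta = 0.1 in the sample-size section may take the result as fair evidence of no effect. Nothing in the article supports that reading.

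There is a second, smaller difficulty. Delta must be a difference between arm means. The number entered, 2.0, is the same as the limit below which one patient's SDBG counts as normal. No expected arm means or other rationale are printed. The power for SDBG therefore also rests on an unexplained difference, and it falls quickly if the true difference is smaller.

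**Working it through.** **Inputs from section 4.5.7:** sigma = 2.41, delta = 2.0, critical values 1.64 and 1.28, loss 20%. Section 4.5.4 gives 30 per arm.

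**1. Reproducing the plan's figure.**
n per arm = 2 × (1.64 + 1.28)² × 2.41² / 2.0² = 24.76.
This matches exactly. The value 1.64 is the one-sided 5% point. With 1.96 in its place the formula gives 2 × (1.96 + 1.28)² × 2.41² / 2.0² = 30.5, so 31 per arm. The printed figure is therefore a one-sided calculation for SDBG, with a standardised effect of 2.0 / 2.41 = 0.83.

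**2. What carries over to Doppler.** Nothing can be computed from the article, because it gives no Doppler difference, SD or rate. What can be stated is the standardised effect that the planned numbers would detect, assuming one continuous Doppler measure compared by a two-sample t test. With 20% loss, 30 × 0.80 = 24 per arm are evaluable. Noncentral-t results, two-sided 5%:

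| Evaluable per arm | Detectable at 80% power | Detectable at 90% power |
|---|---|---|
| 24 | 0.83 SD | 0.96 SD |
| 30 | 0.74 SD | 0.85 SD |

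The normal approximation agrees closely: for 24 per arm and 90% power, (1.96 + 1.28) × √(2/24) = 0.94 SD.

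At assumed effects (the article gives none), 24 per arm and two-sided 5%, power is 17% at 0.3 SD, 40% at 0.5 SD and 77% at 0.8 SD.

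**3. Sensitivity of SDBG power to delta.** Sigma is 2.41 throughout, with 24 per arm and a noncentral-t calculation:

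| True difference (mmol/L) | Two-sided 5% | One-sided 5% |
|---|---|---|
| 2.0 | 80% | 88% |
| 1.5 | 56% | 68% |
| 1.0 | 29% | 41% |

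The first row separates the causes. At the planned difference, having 24 per arm instead of 25 and using the t distribution brings one-sided power to 88%. Two-sided testing brings it to 80%. Only the movement down each column is due to a smaller true difference.

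**The case against.** **The article never claims 90% power for Doppler.** This is correct. Section 4.5.7 gives beta = 0.1 and openly ties it to SDBG. That the figure covers the primary outcome is something a reader might infer from finding a single calculation in the article. The documents do not say so, and no such claim exists to be withdrawn. Nor can one say that Doppler power is low. It is simply not established.

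**Delta may come from the cited treatment studies.** A reader might conclude that delta was derived from the normal limit. The equal value makes this likely, but the text does not state it. The same sentence introduces sigma = 2.41, which cannot come from a normal limit, and section 4.5.7 describes delta only in general terms. It is also tempting to call a 2.0 mmol/L difference implausible because SDBG cannot be negative. That does not follow: no baseline mean is given, and the treated mean need not fall in the normal range. What stands is that no justification is shown.

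**24 per arm is the pessimistic end.** This is fair. Section 4.6.7 expects dropout below 15% and keeps dropouts in the analysis, and the full analysis set in section 4.9.8 uses the final observation for those who stop early. Results for 30 per arm are therefore shown as well.

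**The Discussion already concedes that the sample is not large enough.** It does, but without saying that the calculation concerns a secondary outcome.

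**The full protocol may hold more.** The point does not depend on an omission. The article prints a sample-size justification that does not match its own primary outcome.

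**Conclusion.** The point holds. The arithmetic in section 4.5.7 is correct, but it sizes the trial for SDBG at one-sided 5%, whereas the article ranks Doppler ultrasound as primary. The implied 90% power is not established for the primary outcome. If one continuous Doppler measure is used and tested two-sided at 5%, 90% power requires an effect of 0.85 SD (30 per arm) to 0.96 SD (24 per arm), and 80% power requires 0.74 to 0.83 SD. These figures would not apply to a graded or categorical feature. Section 4.8.1 lists four features without choosing one, and section 4.9.8 provides rank-sum and chi-square tests for such data.

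On delta, the supported conclusion is limited: 2.0 equals the normal limit for a single patient and has no other printed justification as a difference in means. The mismatch of outcomes carries the point; the delta issue is secondary.

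**What to change.** With no change in enrolment:

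1. State in section 4.5.7 that the calculation applies to SDBG, a secondary outcome, at one-sided 5%, and that beta = 0.1 does not carry over to the primary outcome.
2. Designate one continuous measure from the Doppler examination already planned, for example intima-media thickness, as the primary variable. State what the trial can detect on it at two-sided 5%: about 0.83 SD (80% power) and 0.96 SD (90%) with 24 evaluable per arm, or 0.74 and 0.85 SD with all 30.
3. Describe delta = 2.0 as an assumed difference between arm means, and print the SDBG power table above beside it, labelled with sidedness and number per arm.

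The cost is protocol wording and the choice of one primary variable from an examination already scheduled. The downside is that the stated power becomes less favourable.

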#### Suspension criteria

4.6.7

1.Occurrence of serious safety problems during the test;2.Suspension ordered by the administrative department.

Researchers should strive to contact the participants to ascertain the reasons for dropping out from the study, and to acquire other relevant information such as the last time that they had taken the decoction, and to convince them to finish the examinations as far as they possibly can. If the participants experience any AEs during the study, researchers should provide appropriate treatment for them. The expected dropout rate should be <15%. The dropout cases will be included in the statistical analysis.

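### The sample size rests on an undeclared one-sided 5% point and multiplies by 1.2 for 20% loss, so 60 enrolled leave 48 with complete data against the plan's own minimum of 50

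*Protocol article*

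**What the plan says.** Section 4.5.7 uses the formula for comparing two means. The error rates are given as "that is 0.05, β = 0.1", and the tabled values as "t*0.05 = 1.64, *t*0.1 = 1.28". The planning variable is SDBG, with "then σ = 2.41, δ = 2.0". The result is reported as "the value of n brought into the formula is about 24.76", "so the minimum sample size for this test is 50 cases". The allowance for attrition follows: "The estimated lost follow-up rate is 20%, and the final number of cases included is 60".

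The Randomization section (4.5.4) carries the total forward: "According to the 1:1 random arrangement of the treatment and control group, 30 cases in each group".

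Three other places bear on the point:

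- Section 4.6.7 (Suspension criteria) gives a different attrition figure, "The expected dropout rate should be <15" per cent, and adds that dropouts stay in the statistical analysis.
- Section 4.9.8 plans t tests for measurement data without stating sidedness. It defines a full analysis set in which the final observation stands in for patients who do not complete treatment, and a per-protocol set.
- Sections 4.8.1 and 4.8.2 make arterial Doppler ultrasound the primary outcome and SDBG a secondary one.

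**The concern.** Section 4.5.7 is the only justification given for 60 patients, and it claims a type II error of 10%. If the critical value does not match the test that will be reported, or if the attrition step does not preserve the required number, that claim is not met. A non-significant SDBG comparison could then be given more weight as evidence of no effect than the design supports. The sidedness cannot be set aside as a detail for a later document, because the article itself fixes 1.64 and derives enrolment from it.

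**Working it through.** **Inputs** (all from section 4.5.7): δ = 2.0 mmol/L, σ = 2.41, values 1.64 and 1.28, 20% loss, 60 enrolled. Allocation is 1:1 (section 4.5.4). The formula is a figure that is not shown; the standard one is n per group = 2 × [(z_α + z_β) × σ/δ]².

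**1. Reproduce the plan's figure.** 2 × (1.64 + 1.28)² × (2.41/2.0)² = 2 × 8.5264 × 1.4520 = 24.76. This matches exactly; rounded up it is 25 per group, 50 in total.

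**2. Which test does that imply?** 1.64 is the one-sided 5% point. With the two-sided value, 2 × (1.96 + 1.28)² × (2.41/2.0)² = 30.49, so 31 per group and 62 with complete data. The stated figure cannot come from a two-sided 5% test.

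**3. The allowance for loss.**

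- 50 × 1.2 = 60 reproduces the stated total.
- 60 × (1 − 0.20) = 48, or 24 per arm: below 50 in total and below 24.76 per arm.
- To keep 50 after 20% loss: 50/0.8 = 62.5, so 63, or 64 for equal arms. Starting from the unrounded 2 × 24.76 = 49.52 gives 61.9, so 62, which is still above 60.
- 60 enrolled keeps 50 only if loss is at most 10/60 = 16.7%. At 15% loss, 60 × 0.85 = 51.

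**4. Power for SDBG** at δ = 2.0 and σ = 2.41. The noncentrality is (2.0/2.41) × √(n/2); power is given by normal approximation / noncentral t.

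| Complete data | Per arm | One-sided 5% | Two-sided 5% |
|---|---|---|---|
| 48 (20% loss) | 24 | 89.1% / 88.2% | 82.0% / 80.4% |
| 51 (15% loss) | 25.5 | 90.6% / 89.9% | 84.2% / 82.8% |
| 60 (no loss) | 30 | 94.2% / 93.7% | 89.5% / 88.5% |

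The two-sided column stays below 90% in every row, including no loss. Most of the gap comes from the critical value. Going from 25 to 24 per arm costs about one percentage point one-sided (90.1% to 89.1%, normal).

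**The case against.** Four points can be made for the plan.

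**Sidedness.** The document never says the test is two-sided. On the only critical value it gives, 24 per arm has 88–89% power, close to the target. This stands: a reader might infer that the trial has 80% power rather than 90%, but the text supports that only on the condition that the t tests are two-sided. What remains is that a one-sided value drives the enrolment and no one-sided hypothesis is declared.

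**Dropouts stay in the analysis.** Sections 4.6.7 and 4.9.8 retain them, with the final observation used, so the full analysis set at 20% loss may lie anywhere between 48 and 60. This also stands: a reader might take 48 as the number to be analysed, but it is the number with complete data. It does not rescue the attrition step. Section 4.5.7 adds patients because some will be lost, and then adds too few. A carried-forward value does not replace the missing information, and the full analysis set requires follow-up records that an early dropout may lack.

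**Two attrition figures.** One might count 20% against under 15% as a further calculation error. The wording in section 4.6.7 reads as a target for conduct and the 20% as a cautious planning allowance, so this is a mismatch to explain. At 15% loss the plan's minimum of 50 is kept.

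**Importance.** The attrition slip alone is two patients, and the discussion already concedes that the sample is not large enough. That is fair, and it lowers the severity. A general remark about size does not, however, correct a specific statement of 10% type II error.

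**Conclusion.** The point holds in a limited form and should be fixed; it does not rise to a must-fix. Without any added assumption, the attrition step fails the plan's own criterion: 48 with complete data against a minimum of 50. The required number also depends on a one-sided critical value that is nowhere declared.

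The size of the power shortfall is conditional. At 20% loss, type II error is about 11–12% if the test is one-sided and about 18–20% if it is two-sided. With all 60 analysed and a two-sided test it is 10.5–11.5%, so the stated 10% is then missed at every loss rate.

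These figures take δ = 2.0 and σ = 2.41 as given, and they treat lost patients as contributing nothing. They concern SDBG only. A reader might be tempted to read them as the power of the primary comparison, but no planning value for the Doppler outcome is given, so they say nothing about it.

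**What to change.** Keep 60 and correct the text:

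1. Declare the sidedness of the test in sections 4.5.7 and 4.9.8, and use the matching critical value.
2. Reconcile the 20% allowance with the target below 15% in section 4.6.7, for example by saying that one is for planning and the other for conduct.
3. State the number with complete data as 60 × (1 − loss), which is 48 at 20% or 51 at 15%, and note that the full analysis set may be larger because final observations are carried forward.
4. Restate power to match: two-sided, about 80–82% at 20% loss and 83–84% at 15%; one-sided, about 88–89% at 20%.
5. Say that these figures apply to SDBG, a secondary outcome, and not to the Doppler primary outcome.

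The cost is protocol wording and a less favourable stated power, with no added enrolment. For comparison, holding 90% power two-sided at 20% loss would take 62/0.8 = 77.5, so 78 patients; that is not what is proposed.
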